#### Procedure

Participants will be recruited through a hybrid campaign combining traditional media, targeted social media advertisements, and personal contacts. Interested individuals will be directed to a landing page with a brief study description and a link to a detailed study overview and informed consent form. Those who consent to the terms and meet the inclusion criteria will proceed to the baseline assessment (T1). Participants who complete T1 will be randomized in 1:1 blocks to either the intervention or control condition. Participants will be blinded to the allocation. After randomization, they will receive access to their assigned program. Following the intervention period, all participants will be asked to complete a posttest assessment (T2) followed by assessments after 3 (T3) and 6 months (T4). Participant flow is illustrated in Figure 2.

**Figure 2 figure2:**
[figure not shown]
Study flow.

#### Meta Self-Efficacy Intervention

Following the definition of meta self-efficacy, the intervention will guide participants through understanding the mechanism of self-efficacy, introduce and practice meta self-efficacy strategies (leveraging the 4 sources), and foster the development habits that support the use of these strategies in everyday life. The intervention spans 3 weeks and consists of three components: (1) preparation stage and monitoring of daily challenges and self-efficacy beliefs, (2) learning to leverage self-efficacy sources, and (3) incorporating meta self-efficacy strategies in daily life. The intervention is grounded in the work on self-efficacy sources by Bandura [16]. All activities will be evaluated during the co-creation phase to reflect authentic strategies that individuals use to draw on self-efficacy sources. Crucially, the intervention will be tailored to young employees, ensuring that the activities are relevant to both workplace challenges and the experiences of individuals in early adulthood.

In component 1, participants will engage in monitoring and reflecting on their context-specific self-efficacy levels and describe situations associated with them. They will select and optionally reflect on the sources of their specific beliefs, choosing from the 4 self-efficacy sources. In component 2, participants will learn new meta self-efficacy strategies based on leveraging self-efficacy sources. Activities will guide them through reflecting on potential future challenges and enhancing their self-efficacy through leveraging the sources (ie, using meta self-efficacy strategies). For example, this means identifying a role model similar to oneself, seeking persuasion from someone, or recalling and rephrasing a past successful strategy. This component will be strongly dependent on the results of the co-creation phase. Participants will also revisit the challenges they identified in component 1. In this activity, they select a self-efficacy source to target for a specific challenge and plan a strategy for tapping into it, including a backup strategy based on another source. While examples will include actual meta self-efficacy strategies proposed by participants in the co-creation phase, the activities themselves will be subject to refinements resulting from their feedback. Component 3 involves periodic self-efficacy assessments and the application of self-efficacy strategies in real-life situations. High self-efficacy ratings will prompt participants to reflect on the context and sources contributing to a specific type of self-efficacy, whereas low ratings will prompt and lead through applying meta self-efficacy strategies. If necessary, participants will receive contextually relevant examples and boosters of component 2.

The intervention will be self-administered and delivered online [19]. A previous study tested a self-efficacy–based intervention delivered solely using a chatbot on Meta’s Messenger [34]. While effective, this format likely reduced deep engagement. To address this, this intervention integrates web- and chatbot-based exercises. All participants will first access the intervention through a link to a chatbot on Meta’s Messenger. The chatbot will primarily guide them through low-effort tasks [35], forming the core of the first and third components, which rely on text-based activities and optional voice recordings. For selected, more complex activities, primarily in the second component, the intervention will provide direct links to a web platform that can be accessed directly within the Messenger app. Completion of the full intervention will require engagement with both the chatbot and web-based components. Participants will be able to access the intervention on any device, including desktop and mobile, providing a flexible delivery format. Engagement and adherence will be monitored through back-end logs, including records of the number of completed activities and modules and the total volume of text entered for text-based activities, with the option of including more metrics depending on the results of the co-creation phase.

In the control condition, participants will receive access to educational content on occupational health and well-being. This educational content will be delivered via the same platforms as the intervention in the experimental condition and will be matched in intensity. The educational materials will provide evidence-based information on topics related to the trial outcomes, including aspects of work stress in young employees [5,8], psychological processes associated with coping with stress, and important resources related to occupational well-being [10,27].

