#### Sample

The trial will be conducted with a sample of young employees aged 18 to 30 years, representing the early adulthood life stage [2]. To participate in the RCT, individuals must meet the following inclusion criteria: (1) age between 18 and 30 years, (2) professional activity for at least 2 months before trial recruitment (minimum part-time employment or 20 hours per week), and (3) completion of the baseline assessment. Individuals who participated in the co-creation phase focus groups will not be eligible to participate in the RCT phase due to prior exposure to the intervention content and concepts.

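### Both programs are entered through Messenger, but eligibility does not require Messenger and randomisation precedes program access, so the plan can randomise people with no route into either arm

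*Protocol article*

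**What the plan says.** **Entry to the programs.** The Meta Self-Efficacy Intervention section says "All participants will first access the intervention through a link to a chatbot" on Meta's Messenger. The chatbot carries the core of the first and third components. More complex activities, mainly in the second component, are reached by web links that the intervention supplies. The section adds: "Completion of the full intervention will require engagement with both the chatbot and web-based components". The control content is "delivered via the same platforms as the intervention in the experimental condition". No other entry route is described for either arm.

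**Eligibility.** The Sample section of the RCT phase gives a numbered list: age 18 to 30, at least 2 months of work at the stated minimum hours, and "3) completion of the baseline assessment". It adds one exclusion, for people who took part in the focus groups. Messenger is not mentioned.

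**Order of steps.** The Procedure section says "Participants who complete T1 will be randomized in 1:1 blocks to either the intervention or control condition", and access to the assigned program is given after that. Recruitment uses traditional media and personal contacts as well as social media advertisements.

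**Analysis and aim.** Under Intervention Efficacy, everyone randomised is analysed. Under Outcome Measures, outcomes come from an online survey at every time point. Study Aims describes the goal as the basic effect that the intervention can produce, compared with placebo.

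**The concern.** Entry depends on one commercial messaging platform, and nothing in the stated eligibility or procedure establishes before allocation that a participant can or will use it. The recruitment channels do not ensure it either. A person without Messenger can therefore meet every listed criterion, complete baseline and be randomised to a program that they cannot open.

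If such a person still answers the surveys, they contribute outcomes but no intervention effect. The estimate then moves towards the effect of offering the program and away from the effect that the program can produce, which is the stated target. Power planned for d=0.25 is spent on people who could not show the effect. The analysis cannot cleanly recover this. The planned per-protocol comparison selects on behaviour after randomisation, so it loses the protection of the random allocation.

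**Working it through.** **1. The plan's own figure.** The Power Analysis section gives 600 participants for d=0.25, α=.05, power 0.90, 4 measurement points and 30% dropout.

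- A two-sided single-endpoint comparison needs 337 per arm, or 674 in total; 674/(1 − 0.30) = 963. This does not match, but the plan uses a mixed model, so it is not the right benchmark.
- A four-wave random-intercept model with a linear time-by-group effect and 30% dropout accruing linearly needs about 626 at an intraclass correlation of 0.6 and about 474 at 0.7.

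The article does not give the correlation or variance inputs. So 600 is reachable under plausible values and is neither confirmed nor refuted here. The steps below take the stated 90% power at 600 as given and do not depend on reproducing it.

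**2. Dilution formula.** Let f be the share of people contributing outcomes who never entered their program. The barrier exists before allocation and is the same for both arms, so f is taken as equal in the two arms. With no program effect in non-entrants and an unchanged standard deviation:

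- d under intention-to-treat = 0.25 × (1 − f)
- power = Φ[(1.960 + 1.2816) × (1 − f) − 1.960] = Φ[3.2415 × (1 − f) − 1.960], two-sided α assumed because the article does not state sidedness
- total N that restores 90% power = 600/(1 − f)²

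**3. Results.** The article gives no value for f, so every row after the first is an assumption.

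| f (assumed) | d under intention-to-treat | Power at N=600 | N for 90% power |
|---|---|---|---|
| 0 | 0.250 | 0.90 | 600 |
| 2% | 0.245 | 0.89 | 625 |
| 5% | 0.2375 | 0.87 | 665 |
| 10% | 0.225 | 0.83 | 741 |

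Example for 10%: 3.2415 × 0.90 = 2.917; 2.917 − 1.960 = 0.957; Φ(0.957) = 0.83.

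**4. Who counts towards f.** Preliminary Analyses defines dropout as attrition to posttest. A non-entrant who also skips the posttest is a dropout, already within the 30% allowance, and adds missing data. Only a non-entrant who keeps answering counts towards f, and the allowance does not cover that person. The article does not say how survey invitations are sent. If they went only through the chatbot, f would be close to zero and these people would be dropouts.

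**The case against.** The best case against the point has four parts.

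**The article is condensed.** Interested people are sent to a detailed study overview and consent form before baseline. Those materials are not shown and may say that delivery is by Messenger, in which case non-users could decline in time. This stands to a degree: a reader might infer that participants discover the barrier only after allocation, and the article does not support that. However, disclosure is not an eligibility criterion, and the numbered list in the Sample section reads as complete.

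**Residual non-entry may be very small.** RCT participants are not reimbursed, and someone who signed up for a program and could not open it may simply not return. The 30% allowance also rests partly on an earlier self-efficacy trial that the article describes as delivered solely by a Messenger chatbot. This stands as a reason not to treat the table as a forecast. It does not cover people who keep answering.

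**The target effect is already modest.** The effect was lowered from about 0.5 to 0.25. The stated reason is the shift in what the intervention targets, not non-entry. If 0.25 is read as the effect after dilution, power stays at 90%, but the effect among those who enter must then be 0.25/(1 − f): about 0.26 at 5% and 0.28 at 10%.

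**Access is flexible.** The article says "Participants will be able to access the intervention on any device, including desktop and mobile". That concerns hardware and does not remove the need for Messenger.

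Two further readings should be resisted. Intention-to-treat does not count non-entrants as treated; it analyses them as randomised and validly estimates the effect of offering the program. Nor is missing credibility data for non-entrants a defect, because the Other Metrics section deliberately defines credibility as arising after first exposure.

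**Conclusion.** The gap holds. As written, the article can randomise people with no route into either program, and this sits poorly with an efficacy aim. For the control arm, entry through Messenger is inferred from the shared platforms, which is a reasonable reading.

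The consequence is loss of sharpness, not invalidity. Each 1% of outcome-providing participants who never entered lowers the intention-to-treat effect by 1%. Power falls from 90% to about 89%, 87% or 83% at assumed rates of 2%, 5% or 10%. These figures assume equal non-entry in both arms, no effect without entry, two-sided testing and the plan's own 90% as the starting point. A reader might infer a large power loss; the article gives no non-entry rate, so no particular loss can be claimed.

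The point is a cheap improvement, worth making because the remedy is nearly free before recruitment and the problem cannot be cleanly repaired afterwards.

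**What to change.** Add a criterion to the RCT Sample section: the participant has a Messenger account and is willing to use it for the study. Screen it with the other criteria, before the baseline assessment and randomisation, and carry the change into the trial registration. Keep the intention-to-treat analysis. State that non-entry will be counted from the back-end logs and reported by arm.

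As an optional extra, confirm access before allocation by having each person open a chatbot link that is the same for both arms, and then release the assigned program. This precedes allocation and leaves blinding and intention-to-treat intact. It also adds a step that may lose sign-ups in a trial whose Discussion names recruitment as the main risk, so it is the team's choice.

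The cost of the core change is one screening question, slightly narrower generalisability (to Messenger users) and some loss of sign-ups before randomisation. RCT recruitment was scheduled for the beginning of 2026. If it has already begun, the criterion can apply only to later entrants and should be documented as a deviation, and reporting non-entry by arm becomes the main safeguard.

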#### Outcome Measures

##### Overview

All outcome measures will be assessed at all time points via an online survey. The primary outcome is work self-efficacy. Secondary outcomes include 3 dimensions of occupational well-being: job stress, job affective well-being, and work capabilities. Meta self-efficacy will be measured as a manipulation check.

##### Work Self-Efficacy

The primary outcome is work self-efficacy, measured using the Work Self-Efficacy Scale [36]. Psychometric analyses of the Work Self-Efficacy Scale have revealed a robust bifactor structure—with a global work self-efficacy factor and 4 specific subdimensions—and demonstrated excellent reliability (ω=0.96 for the global factor and 0.67-0.76 for the specific subdimensions), thereby supporting its validity for assessing work-related self-efficacy. The questionnaire consists of 26 items, with responses ranging from 1 (“not at all”) to 7 (“completely”). The overall score will be calculated as a mean.

##### Job Stress

Job stress will be measured using the Perceived Stress Scale [25]. This 4-item questionnaire assesses the frequency of perceiving stress. We will use a version of the tool contextualized to reflect job stress, which has shown high reliability in a previous study (Cronbach α=0.87 to 0.89 [15]). Responses range from 0 (“never”) to 4 (“very often”), with the overall score calculated as a mean.

##### Job Affective Well-Being

Job affective well-being will be measured using the Job-Related Affective Well-Being Scale [26]. We will use a 12-item version that has demonstrated good reliability (Cronbach α=0.64 to 0.79) and a 4-factor structure: high pleasure and low arousal, high pleasure and high arousal, low pleasure and low arousal, and low pleasure and high arousal [37]. Responses range from 0 (“never”) to 5 (“extremely often or always”), and scores are averaged across positive and negative emotions.

##### Work Capabilities

Work capabilities will be measured using the Capability Set for Work Questionnaire [11,27], which is a set of questions assessing capabilities important for sustainable employability. The questionnaire consists of 7 statements and has demonstrated high reliability in a previous analysis (ω=0.77 [38]). Each capability is rated on 3 aspects: importance (whether a certain capability is valued as important), opportunities (whether one has the opportunities related to a certain capability), and success (whether one can succeed in realizing a certain aspect of work). Responses range from 1 (“not at all”) to 5 (“very much”). A global score will be calculated as the mean of the 7 items.

##### Meta Self-Efficacy

In line with the theoretical mechanism of the intervention, meta self-efficacy will be measured as the manipulation check. It will be assessed using a 13-item meta self-efficacy scale [18] encompassing 4 factors that represent leveraging each of the 4 self-efficacy sources: mastery experiences, vicarious experiences, persuasion, and emotional and physiological states. Each item starts with “When I need to, I can...” and is followed by a statement related to 1 of the 4 sources. Example items for each factor are “think about situations where initially I felt I couldn’t cope, but eventually managed to” (mastery experiences), “observe someone similar to me who copes despite encountering obstacles” (vicarious experiences), “believe others when they convince me that I will overcome obstacles and manage” (persuasion), and “interpret tension and stress in a difficult situation as a signal that I will manage” (emotional and physiological states). Psychometric evaluations have demonstrated high reliability (overall Cronbach α=0.91) and support the 4 theory-informed factors as part of a bifactor scale structure [18]. The general score will be calculated as a mean.

##### Other Metrics

Other metrics will assess treatment credibility, usage, engagement, and adherence. Treatment credibility will be operationalized as emergent credibility and measured after initial intervention exposure during the first module. We will assess credibility using the Credibility/Expectancy Questionnaire, which has shown high reliability (Cronbach α=0.85) [39]. The questionnaire items will be contextualized to reflect participation in an internet intervention. Use and engagement metrics will include completed components, completed activities, log-ins, activities per log-in, total time spent, and total words written [40]. Adherence will be defined and measured as the percentage of completed intervention activities. Additionally, we will measure subjective adherence using the following question at the posttest time point: “How accurately, in your opinion, have you completed all tasks? For example, did you follow the instructions, reflect on the questions, and respond to them exhaustively?” [22,41].

#### Statistical Analyses

##### Preliminary Analyses

We will conduct preliminary analyses, including a randomization check and dropout analysis, using ANOVAs and chi-square tests, as well as examine differential attrition through 2-tailed *t* tests. Dropout will be operationalized as attrition to posttest. Additionally, we will assess intervention-related adherence and engagement metrics (see the Other Metrics subsection).

##### Intervention Efficacy

The intervention’s efficacy will be evaluated for each outcome measure following the intention-to-treat principle, meaning that all randomized participants will be included in the final analysis. The primary efficacy analysis will use a linear mixed-effects model, with a random intercept for participants and fixed effects of time and condition [42]. Although the expected dropout rate is included in our a priori power analysis, we will also examine the actual dropout rate and its characteristics. This examination will determine whether there is a significant difference in dropout percentages between the 2 conditions, a phenomenon known as differential dropout [43]. Subsequently, we will apply an appropriate missing data imputation method and calculate pooled results using linear mixed-effects models (eg, using the *mice* and *mitml* R packages [44]). Sensitivity analyses will be conducted to examine the robustness of the results and compare intervention effect estimates across per-protocol, intention-to-treat, and imputed data analyses. Additionally, we will verify the credibility of the placebo in comparison to the intervention condition.

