In the RCT phase, we will test the intervention’s efficacy comparing the meta self-efficacy intervention to a placebo. The goal is to assess the basic effect that the meta self-efficacy intervention can produce while controlling for the expectation bias [24]. We will additionally compare treatment credibility between conditions. Although meta self-efficacy is potentially applicable universally across life domains, testing its enhancement within the framework of the theory by Bandura requires concentrating on a specific background. In particular, enhancing meta self-efficacy should, in principle, lead to improvements in domain-specific self-efficacy. In this study, we test the effects of improving meta self-efficacy in the occupational context and among young employees, expecting that enhancing meta self-efficacy will improve their work self-efficacy (primary outcome). Furthermore, strengthening meta self-efficacy should lead to further well-being benefits [10], which we will measure as multiple dimensions of occupational well-being. These will reflect job-related emotions, stress levels, and work capabilities, encompassing behaviors and values. Accordingly, the secondary outcomes include job stress [25], job affective well-being [26], and work capabilities [27]. We expect improvements in both primary and secondary outcomes immediately after the intervention, with effects sustained at follow-ups. Additionally, a secondary objective of the RCT phase is to examine how factors such as intervention engagement and adherence relate to the intervention’s efficacy.

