### RCT Phase

#### Study Design

To evaluate the efficacy of the meta self-efficacy intervention, we will conduct a 2-arm RCT. Participants will be randomly assigned (1:1) to 1 of 2 conditions: an experimental group with access to the meta self-efficacy–enhancing internet intervention or a placebo control group with access to educational content. A placebo comparator in the form of interactive educational content on occupational well-being has been chosen over a waitlist control [31] to avoid a typical expectation bias: participants in the intervention group usually expect improvement, whereas those on the waitlist do not. An active but nontherapeutic comparator delivered through the same modality as the intervention [24] will allow us to isolate the specific effect of the meta self-efficacy intervention while holding expectations similar in both groups. Outcomes will be measured at 4 time points: baseline, posttest, and 3- and 6-month follow-ups.

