#### Power Analysis

To determine the required sample size, we considered the effect sizes reported for internet interventions aimed at enhancing context-specific self-efficacy. These interventions have shown effect sizes of approximately *d*=0.5 for various stress-related outcomes [20,32]. However, the effect size for the meta self-efficacy intervention may differ and is likely smaller as it shifts the focus from enhancing self-efficacy in a specific context to bolstering the ability to leverage self-efficacy sources. To account for this, the trial is powered to detect a minimum meaningful effect of *d*=0.25. We conducted an a priori power analysis for a linear mixed-effects model using the *powerlmm* R package (R Foundation for Statistical Computing) [33]. Given 4 measurement points, an error level of α=.05, and power of 1 – β of 0.90, the analysis indicates that 600 participants are needed. This calculation factors in a 30% dropout rate based on a previous self-efficacy internet intervention for young adults and a broader review of adherence in mobile interventions [21,34].

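### As written, the primary model has no time-by-condition term or baseline adjustment, so its condition effect averages in the pre-randomisation visit and shrinks a sustained effect to 75% or less

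*Protocol article*

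**What the plan says.** The Intervention Efficacy section of the protocol article gives the only specification of the primary analysis: "The primary efficacy analysis will use a linear mixed-effects model, with a random intercept for participants and fixed effects of time and condition". No other section adds an interaction, a baseline covariate, a baseline constraint or a named post-baseline contrast. The Discussion says only that the main analysis concerns differences between groups.

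Three other sections settle what enters that model:

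- Study Design: "Outcomes will be measured at 4 time points: baseline, posttest, and 3- and 6-month follow-ups".
- Outcome Measures, Overview: "All outcome measures will be assessed at all time points via an online survey".
- Procedure: "Participants who complete T1 will be randomized in 1:1 blocks to either the intervention or control condition". T1 is therefore a pre-randomisation measurement.

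Study Aims gives the expected shape of the effect: "We expect improvements in both primary and secondary outcomes immediately after the intervention, with effects sustained at follow-ups". Under Power Analysis, "the trial is powered to detect a minimum meaningful effect of" d=0.25. With four measurement points, alpha .05, power 0.90 and 30% dropout, "the analysis indicates that 600 participants are needed". That section does not give the within-person correlation, the contrast that was powered, the visit to which d refers, or the timing of the dropout.

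**The concern.** At T1 nobody has been allocated, so the expected difference between arms is zero. If the only term involving allocation is a main effect of condition, the model fits the same arm difference at all four visits, and the T1 zero is averaged into what is reported as the intervention effect. Participants lost before T2 make this worse, since they contribute a T1 value and nothing else.

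The model also has no parameter that answers the question in Study Aims. One constant cannot separate a difference at posttest from a difference at 3 or 6 months.

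At stake are the size of the primary estimate, the chance of detecting the effect the trial was sized for, and the freedom left to the analyst. If the term is added only once results are visible, the primary test could become the T2, T3 or T4 difference or an average.

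**Working it through.** **Inputs from the protocol article.** 300 per arm (600, 1:1); d=0.25; alpha .05; 30% dropout; four visits including T1; effect pattern (0, d, d, d) from Study Aims.

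**Assumptions.** Two-sided test; total SD 1; within-person correlation rho, not stated and shown as a range; two dropout patterns, equal in both arms: all 30% lost before T2, or cumulative loss of 10%, 20% and 30% at T2, T3 and T4. The random intercept implies the same rho between any two visits.

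**The plan's own figure.** A two-sample comparison at one visit needs 2(1.960+1.282)²/0.25² ≈ 336.2, so 337 per arm or 674 in total, and 674/0.70 ≈ 963 after dropout. That is not 600. A baseline-constrained single-visit contrast comes close at rho about 0.6: 616 with all loss before T2, and 592 for T4 with gradual loss. So 600 is attainable, but the article does not show which contrast or correlation produced it.

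**Model as written.** A participant with k visits carries information k/(1+(k−1)rho) on the condition coefficient. With f_k the fraction having k visits and S_k the sum of the true effects over those visits:

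- coefficient = Σ f_k·S_k/(1+(k−1)rho) ÷ D, where D = Σ f_k·k/(1+(k−1)rho)
- SE = √(2/(300·D))
- power = Φ(coefficient/SE − 1.96)

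Complete data: coefficient = (0+0.25+0.25+0.25)/4 = 0.1875 at every rho.

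Worked case, rho=0.5, 30% lost before T2:

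- D = 0.3×1 + 0.7×4/2.5 = 1.42
- coefficient = (0.7×0.75/2.5)/1.42 = 0.21/1.42 = 0.148
- SE = √(2/426) = 0.0685
- power = Φ(2.158 − 1.96) = 0.58

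Worked case, rho=0.5, gradual loss:

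- D = 0.1 + 0.133 + 0.15 + 1.12 = 1.503
- coefficient = (0.0167+0.025+0.21)/1.503 = 0.167
- SE = 0.0666
- power = Φ(2.514 − 1.96) = 0.71

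| rho | Complete: power | Lost before T2: coefficient, power | Gradual: coefficient, power |
|---|---|---|---|
| 0.1 | 0.98 | 0.165, 0.88 | 0.174, 0.94 |
| 0.2 | 0.95 | 0.160, 0.80 | 0.172, 0.88 |
| 0.3 | 0.915 | 0.156, 0.72 | 0.171, 0.82 |
| 0.5 | 0.83 | 0.148, 0.58 | 0.167, 0.71 |
| 0.6 | 0.78 | 0.144, 0.52 | 0.166, 0.66 |
| 0.8 | 0.70 | 0.137, 0.43 | 0.163, 0.57 |

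At rho 0.6, where a single-visit contrast fits 600, the model as written would need 1,122 (gradual) or 1,556 (all before T2) for 90% power.

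**Baseline kept out of the effect (common T1 mean, 30% lost before T2, 210 per arm at T2).**

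- T2 difference: variance 2(1−rho²)/210. At rho 0.5 this is 0.00714, SE 0.0845, power Φ(2.958 − 1.96) = 0.84. Power is 0.77, 0.89 and 0.95 at rho 0.3, 0.6 and 0.7.
- T2–T4 average: variance 2[(1+2rho)/3 − rho²]/210. At rho 0.5 this is 0.00397, SE 0.0630, power Φ(3.969 − 1.96) = 0.98. Power is at least 0.97 for rho 0.3 to 0.8.

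**The case against.** **The sentence may be shorthand.** A condensed article can list factors without writing out the formula; it nowhere says the model is additive, and the stated aim makes sense only with visit-specific effects. This stands as a reason not to assume that the authors intend a main-effects analysis. It does not clear the text: the article lists the fixed effects, and the list as printed defines a model that estimates the wrong quantity.

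**A reader might infer that the trial cannot have 90% power, or that 600 is wrong.** The document does not support either. The correlation is not given: even the model as written has 91.5% power at rho 0.3 without dropout, and 94% at rho 0.1 with gradual loss. The powered contrast is not named either, so 600 may be sound for a contrast the analysis section fails to mention.

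**Imputation changes the dropout figures.** The same section plans imputation with pooled mixed-model results, without making clear whether that analysis is primary or supportive. If the imputation allows for arm and visit, the further dilution from dropout should largely disappear. The drop to 75% remains, because averaging four completed visits still includes T1.

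**A reader might infer a risk of false claims.** That does not follow. With no effect at any visit the condition coefficient has expectation zero, and its test is valid given a correct covariance and ignorable missingness.

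**Conclusion.** The point holds for the analysis as printed. Under a sustained effect of 0.25 SD, the condition coefficient targets 0.1875 with complete data whatever the correlation. For rho 0.3 to 0.8 with 30% dropout and no imputation it targets 0.137 to 0.171. It carries no information on timing or persistence.

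The power consequence is conditional on the literal reading, on rho and on when dropout occurs. At N=600 with 30% dropout, power is 72% down to 43% (all lost before T2) or 82% down to 57% (gradual) as rho rises from 0.3 to 0.8. Power near 90% needs rho of roughly 0.1 to 0.2 or less. That seems unlikely for a 26-item scale with a reported omega of 0.96, although omega measures internal consistency and not stability over time.

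The sample size is not shown to be wrong. With the baseline kept out of the effect, 600 is ample for the T2–T4 average; for a single visit with all loss before T2 it is about adequate from rho 0.6 upwards.

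**What to change.** In Intervention Efficacy, replace the model sentence with one stating three things:

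1. Time (T1 to T4) is categorical, and the model includes condition-by-time.
2. T1 is handled as a common or adjusted baseline. A constrained baseline, T1 as a covariate with T2 to T4 as outcomes, or an ordinary time-by-condition model with named contrasts are all acceptable. They differ in power: at rho 0.5 with gradual loss, the T2 contrast has 92% with a constrained baseline and 84% as an ordinary T2-minus-T1 interaction.
3. One post-baseline contrast is primary, for example the T2 difference or the T2–T4 average.

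In Power Analysis, confirm or restate the power of 600 for that contrast, giving the assumed within-person correlation and the dropout pattern.

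If an interaction was always intended, this only corrects the published sentence. The cost is a sentence or two and one rerun of the power calculation, with no added participants or assessments. It should be done before outcome data by arm are seen.
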